### Sample size calculation

The sample size calculation is based on the rate of steroid resistant rejection after OLT. According to the pooled estimate of a Cochrane meta-analysis the incidence of steroid resistant rejection in patients with a CNI based immunosuppressive regimen may be inferred as 12.61% with a 95%-confidence interval of [6.36, 18.65] (estimated by bootstrap methods) [25]. To minimize the sample size for this therapeutic exploratory trial the study is designed as a non-controlled, prospective, two-stage study. In this two stage design [26] superiority of the safety or efficacy rate to the required minimum or "uninteresting" rate *p*_0 _will be tested in stage I. If the treatment is inferior to *p*_0 _the trial will be halted and no further patients enrolled, whereas if the treatment is superior to *p*_0 _stage II will be entered. In stage II the rate will be compared to the actual target rate *p*_1_. For the present trial *p*_0 _and *p*_1 _have been fixed at 0.8 and 0.95 respectively. With error probability *α *= 0.05 and power *β *= 0.2 the required sample sizes for stage I and II are *n*_0 _= 9 and *n*_1 _= 20 respectively. The maximum success rates that corroborate inferiority of the regimen to the fixed rates *p*_0 _and *p*_1 _have been calculated as *r*_0 _= 7 and *r*_0 _+ *r*_1 _= 26, meaning that if more than 7 patients in stage I and 26 patients in stage II do not experience a steroid resistant rejection the true response is at least the target level *p*_1 _(see Figure 2).

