**Figure 2 F2:**
[figure not shown]
**Flow chart of the CILT study**. Derived from an optimal two-stage design for a phase II clinical trial with the following parameters: *p*_0 _= 0.8, *p*_1 _= 0.95, error probability *α *= 0.05, and error probability *β *= 0.2. Abbr.: *n*, number of patients; *r*, maximum number of responders at which *H*_0 _will not be rejected; *H*_1_, alternative hypothesis.

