### Statistical analysis plan

The confirmatory analysis will be performed for the per-protocol population. All statistical analyses will be performed with a type I error *α *= 0.05 and, where appropriate, a non-inferiority margin of *δ *= -0.1 will be assumed.

All rates will be tested in an approximate one sample design test for non-inferiority [27] against reference values obtained from a pooled meta-analysis of trials with immunosuppressive regimen based on CNI [25].

Confidence intervals will be calculated by the method of Agresti and Coull [28]. The only confirmatory analysis will concern the primary endpoint; all other analyses will be exploratory.

Continuous secondary end-points will be compared to reference values with student's T test unless there is considerable evidence for a non-parametric distribution. Event-time data, i. e., time to acute rejection, patient, and graft survival will be estimated by the Kaplan-Meier method.

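### The two-stage rule is correct for its inputs, but the plan reads too much into a pass or a failure and gives no power for a regimen as good as CNI

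*Protocol article*

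**What the plan says.** All places are in the protocol article.

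- **Sample size calculation, benchmark.** The CNI figure for steroid resistant rejection comes from a meta-analysis and "may be inferred as 12.61% with a 95%-confidence interval of [6.36, 18.65".
- **Sample size calculation, anchors.** "For the present trial *p*_0 _and *p*_1 _have been fixed at 0.8 and 0.95 respectively". The first is described as "the required minimum or 'uninteresting' rate" and the second as the target. No reason is given that links either to the CNI figure.
- **Sample size calculation and Figure 2, design.** "the required sample sizes for stage I and II are *n*_0 _= 9 and *n*_1 _= 20 respectively", with "error probability *α *= 0.05, and error probability *β *= 0.2". I read this as 80% power at p1.
- **Sample size calculation, interpretation.** The cut-offs 7 and 26 are presented as the highest success counts that still support inferiority to p0 and p1. The pass criterion is explained as "meaning that if more than 7 patients in stage I and 26 patients in stage II do not experience a steroid resistant rejection", and the sentence then concludes that the true rate reaches at least p1. I take 26 as the cumulative count, since stage II has only 20 patients and the section writes it as a sum over both stages.
- **Objectives and endpoints.** All endpoints are compared with CNI reference values. The primary endpoint is biopsy-proven steroid resistant rejection within 30 days.
- **Statistical analysis plan.** Rates are tested for non-inferiority against the CNI reference, and "where appropriate, a non-inferiority margin of *δ *= -0.1 will be assumed". Only the primary endpoint is confirmatory.

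**The concern.** The trial asks whether rejection protection stays adequate when CNI is left out. The natural case to examine is therefore a regimen about as good as CNI. The article gives the rule's behaviour only at 80% and 95%, and both lie outside its own interval for CNI. Its power figure thus holds only for a regimen better than every value in that interval.

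The interpretation sentences add to this. A pass would be reported as evidence for 95%, which the test does not address. A failure would be reported as inferiority, although a regimen equal to CNI may well fail. The result is meant to decide whether a phase III trial follows, so both readings would carry into that decision.

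There are also two candidate tests of the primary endpoint, with different null values: the two-stage rule and the non-inferiority test.

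**Working it through.** **Inputs** (sample size section unless noted)
- CNI rejection rate 12.61%, interval 6.36% to 18.65%. Rejection-free: 100 − 12.61 = 87.39%, interval 81.35% to 93.64%.
- p0 = 0.80, p1 = 0.95, alpha 0.05, beta 0.2.
- Rule: continue if at least 8 of 9 succeed, pass if at least 27 of 29 succeed in total.
- Margin −0.1 (Statistical analysis plan).

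**Formula.** With true success rate p,

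P(pass) = P(X1 = 8) × P(X2 ≥ 19) + P(X1 = 9) × P(X2 ≥ 18), where X1 ~ Bin(9, p) and X2 ~ Bin(20, p).

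P(stop at stage I) = 1 − P(X1 = 8) − P(X1 = 9).

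**Step 1: reproduce the plan's design.**
- p = 0.80: 0.3020 × 0.0692 + 0.1342 × 0.2061 = 0.0486.
- p = 0.95: 0.2985 × 0.7358 + 0.6302 × 0.9245 = 0.8024.

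A full search over two-stage designs for these inputs returns 7/9 and 26/29 as both the optimal and the minimax design. The stated design is right.

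**Step 2: the same rule at the plan's CNI rate.**

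P(pass) at 0.8739 = 0.3861 × 0.2623 + 0.2973 × 0.5292 = 0.2586.

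| True rejection-free rate | Meaning | P(stop at stage I) | P(pass) |
|---|---|---|---|
| 0.80 | p0 | 0.564 | 0.049 |
| 0.8135 | lower limit of CNI interval | 0.522 | 0.068 |
| 0.8739 | CNI point estimate | 0.317 | 0.259 |
| 0.9364 | upper limit of CNI interval | 0.108 | 0.696 |
| 0.95 | p1 | 0.071 | 0.802 |

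At the CNI point estimate the trial fails with probability 1 − 0.259 = 0.741. Over the interval, failure runs from 1 − 0.696 = 0.304 to 1 − 0.068 = 0.932.

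**Step 3: what the boundary results show.** Agresti-Coull 95% intervals, the method the plan names (z = 1.96, so n + z² = 32.84 and centre (x + z²/2)/32.84):
- Lowest pass, 27/29 = 0.931: 0.881 ± 0.111, that is 0.77 to 0.99. This does not establish 0.95.
- Highest failure, 26/29 = 0.897: 0.850 ± 0.122, that is 0.73 to 0.97. The observed rate is above both p0 and the CNI reference, and the interval contains 0.80, 0.8739 and 0.95. It does not show inferiority to any of them.

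**Step 4: the two tests side by side.**
- Two-stage rule: null 80%, an implied margin of 87.39 − 80 = 7.39 points.
- Non-inferiority test: null 87.39 − 10 = 77.39%.

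The article does not say which variance its approximate test uses. At n = 29, against a one-sided critical value of 1.645:
- With the null variance, 26/29 gives z = 1.579 and 27/29 gives 2.023, so 27 successes are needed.
- With the estimated variance, 26/29 gives z = 2.169, so 26 successes are enough.

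In the second case a result of 26/29 fails the two-stage rule and passes the non-inferiority test. Power at 0.8739, allowing for the stage I stop, is 26% with the null variance and 43% with the estimated variance. Neither is near 80%.

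**The case against.** The strongest reply is that nothing is miscalculated. Power is always conditional on the chosen alternative, Figure 2 ties alpha and beta openly to 0.80 and 0.95, and the article says that it wants a small exploratory trial. This stands. A reader might infer from the pass probability at the CNI rate that the 80% figure is wrong; it is not.

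A reader might also infer that p0 is a mistake because standard treatment already exceeds it. The documents do not support that. The article also calls p0 a required minimum, and a floor below standard treatment is ordinary for a non-inferiority question. The anchors sit nearly symmetrically about the CNI estimate (7.39 points below, 95 − 87.39 = 7.61 above), just outside its interval. They may have been chosen to bracket it, and the full protocol may say so.

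Nor does the article say that a failing regimen is inferior to CNI. Its wording concerns p0 and p1. Given the declared comparison with CNI, a reader could easily carry that label over, which is why the permitted conclusion should be spelled out.

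The 26% is a point value. It depends on a wide interval and on whether the meta-analysis rate, quoted without a time window, fits the 30-day biopsy-proven endpoint. This stands too, so the range belongs with the figure.

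Finally, setting the estimate and its interval against the CNI reference is already planned and needs no new request.

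None of this rescues the interpretation sentences, supplies the missing power, or reconciles the two null values.

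**Conclusion.** The point holds as one about conclusions and disclosure, not about the arithmetic or the sample size. The rule tests whether the rejection-free rate exceeds 80%, at exact one-sided alpha 0.049. A pass therefore excludes a steroid resistant rejection rate of 20% or more. It does not establish 95% or a benefit over CNI. A stop or a final failure means only that 20% or more was not excluded.

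For a regimen equal to CNI, the chance of passing is about 26%, with a range of 7% to 70% over the plan's own interval, and the chance of stopping after nine patients is about 32%. Even at the favourable end of that interval it stays below 80%. These figures assume that the meta-analysis rate applies to the trial's endpoint, that all 29 patients can be evaluated if stage II is entered, and that outcomes are independent with a constant rate.

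Separately, the two stated tests of the primary endpoint have different null values (80% and 77.39%) and can disagree at 26/29.

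**What to change.** Keep 9 + 20 patients and both cut-offs, and change the text as follows.

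1. **Sample size calculation, interpretation.** Replace the present reading with wording such as: *A pass rejects a steroid resistant rejection rate of 20% or more at one-sided alpha 0.05. It does not establish a 95% success rate or a benefit over CNI. A stage I stop or a final failure means that a rate of 20% or more was not excluded, and does not show that the regimen is inferior to CNI.*
2. **Sample size calculation, power.** State that 80% power holds only if the true rejection rate is 5%. Add that at equality with CNI (12.61%) it is about 26%, ranging from 7% to 70% over the interval for the CNI rate, on the assumption that this rate applies to the 30-day biopsy-proven endpoint.
3. **Statistical analysis plan.** Name either the two-stage rule (null 80%, implied margin 7.39 points) or the non-inferiority test (margin 10 points, null 77.39%) as the single confirmatory test of the primary endpoint, and label the other as supportive. If the non-inferiority test is named, state its variance form and how it allows for the stage I stop.

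The cost is wording and a less favourable stated power. No extra patients are needed.

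### The sample size section reads the two-stage limits 7/9 and 26/29 as evidence of inferiority, continuation as superiority to p0, and a final pass as a true rate of at least p1; the design supports none of these readings, and the Figure 2 caption defines the limits differently

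*Protocol article*

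**What the plan says.** The protocol article's section on sample size calculation sets an uninteresting success rate p0 and a target rate p1, which "have been fixed at 0.8 and 0.95 respectively". Success means no steroid resistant rejection. The section then attaches four conclusions to the counts:

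- **Stage I as a test.** Stage I is said to test "superiority of the safety or efficacy rate to the required minimum", that is, to p0. The trial halts if the regimen is inferior to p0 and goes on if it is superior to p0.
- **Stage II comparator.** The stage II rate is to be compared with p1.
- **Counts at or below the limits.** The limits 7 and 26 are introduced as "The maximum success rates that corroborate inferiority of the regimen to the fixed rates" p0 and p1.
- **Counts above both limits.** These are taken to mean that the true response is at least p1.

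The Figure 2 caption describes the same numbers differently. The scheme is "Derived from an optimal two-stage design for a phase II clinical trial", and r is the "maximum number of responders at which" H0 will not be rejected. The section headed Statistical analysis plan adds: "All statistical analyses will be performed with a type I error" of 0.05.

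**The concern.** In an optimal two-stage single-arm design there is one null hypothesis, here H0: p <= 0.80. It can be rejected only at the end, on all 29 patients. The stage I limit is a futility cut, and the final limit is a non-rejection limit. Failing to reject p <= 0.80 is not evidence that p is below 0.80, still less below 0.95. Passing the futility cut is not evidence that p exceeds 0.80. Rejecting p <= 0.80 is not evidence that p is at least 0.95.

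The article presents the trial as the step that decides whether a phase III trial follows and that supplies its planning figures. If the text is followed, a stopped or negative trial is described as having found inferiority, and a positive one as having reached the 95% target. In each case the description claims more than the data can carry. The error about a positive result matters most, because an assumed success rate of 95% could pass into the next sample size calculation.

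**Working it through.** **Inputs.** From the sample size section and the Figure 2 caption: p0 = 0.80, p1 = 0.95, alpha = 0.05, beta = 0.20 (taken as the type II error, as in the caption), 9 patients in stage I and 20 in stage II, limits 7 (of 9) and 26. The section writes the second limit as r0 + r1, so it is cumulative, out of 29. The CNI reference is 12.61% steroid resistant rejection, so 100 − 12.61 = 87.39% success. All probabilities are exact binomial.

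**1. Reproducing the design.** H0 is rejected if stage I gives at least 8 of 9 and the total is at least 27 of 29:

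P(reject | p) = P(X1 = 8)·P(X2 >= 19) + P(X1 = 9)·P(X2 >= 18), with X1 ~ Bin(9, p) and X2 ~ Bin(20, p).

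- p = 0.80: 0.3020 × 0.0692 + 0.1342 × 0.2061 = 0.0209 + 0.0277 = 0.0486.
- p = 0.95: 0.2985 × 0.7358 + 0.6302 × 0.9245 = 0.2197 + 0.5827 = 0.802.

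An enumeration of designs with total N from 15 to 40 gives 9/29 with limits 7/26 as the optimal design (expected N 17.72 at p0). The stated design is reproduced. The 5% error rate belongs to the whole rule, tested against p0 at the end.

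**2. Stage I stop, read as inferior to p0.**

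- P(X <= 7 of 9 | 0.80) = 0.564, so the result is more likely than not at exactly 0.80.
- Inferiority to 0.80 at one-sided 5% would need at most 4/9 (tail 0.020; 5/9 gives 0.086).
- P(X <= 7 of 9 | 0.8739) = 0.317: a regimen equal to the CNI reference stops almost one time in three.
- P(X <= 7 of 9 | 0.95) = 0.071.

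**3. Continuation, read as superior to p0.**

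- P(X >= 8 of 9 | 0.80) = 0.3020 + 0.1342 = 0.436; at p = 0.70 it is 0.196.
- Even 9/9 gives 0.8^9 = 0.134, so no stage I result can show superiority to 0.80 at the 5% level.

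**4. Final count at or below 26, read as inferiority.** The terms appear in the order p0, p1 and then 7, 26, and stage II is said to be compared with p1. The natural pairing is therefore 26/29 with 0.95.

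- 26/29 = 89.7%, exact 90% interval 75.4% to 97.1%, which contains both 0.80 and 0.95.
- Lower tails against 0.95, taking n = 29 as fixed: 24/29 gives 0.014, 25/29 gives 0.055, 26/29 gives 0.175. A count of 24 or fewer does show inferiority to 0.95 at one-sided 5%; 25 and 26 do not.
- Against 0.80, P(X <= 26 of 29) = 0.948.
- The observed rejection rate at this limit is 3/29 = 10.3%, below the 12.61% reference.

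**5. Final pass, read as a true rate of at least p1.**

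- The smallest passing count, 27/29 = 93.1%, is itself below 95% (exact 95% interval 77.2% to 99.2%).
- The formula in step 1 gives a pass probability of 0.158 at p = 0.85 and 0.414 at p = 0.90.

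**The case against.** The strongest reply is that nothing operational is wrong. The limits, sample sizes and error rates are correct, and the trial stops and passes at the same counts whatever they are called. The stage I stopping rates above are properties of the design, and rewording does not change them. The caption already gives r its proper meaning. The text says corroborate, which is weaker than proof. The analysis section already provides for confidence intervals. All of this stands, and it limits the point to the conclusions drawn from the counts.

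Two stronger readings are tempting, and the article does not support them:

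- **That 26/29 would be reported as inferior to 80%.** A reader might infer this because p0 and p1 are named together and the limits are not explicitly matched to them. The order of terms and the stage II sentence point to 0.95. Only 7/9 is tied to 0.80.
- **That a stage I pass would be published as a superiority finding with a 43.6% error rate in place of 5%.** The section gives a halt-or-continue rule and does not say that such a claim will be reported. The 43.6% shows that the label superior is unearned; it is not a breach of the design's overall alpha.

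The reply does not remove the contradiction between the section and its own figure caption. Nor does it rescue the statement about a final pass, which is wrong on any reading.

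**Conclusion.** The point holds as an error of interpretation attached to a sound design. All four conclusions are unsupported:

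- a stop is not evidence of inferiority to 0.80 (tail 0.564 at the limit);
- continuation is not evidence of superiority to 0.80 (probability 0.436 at exactly 0.80);
- 25 or 26 successes of 29 do not show inferiority to 0.95;
- a pass rejects p <= 0.80 and does not show p >= 0.95.

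The third item is narrow: 24 or fewer of 29 would justify the label against 0.95. It rests on pairing 26/29 with p1 and on treating n = 29 as fixed, without adjustment for the stage I look. The other three need only the stated design parameters. The go/no-go decision is unaffected; what changes is what may be concluded and carried into phase III planning.

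**What to change.** Keep the sample sizes and limits. Reword the sample size section to agree with the Figure 2 caption, for example:

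> One hypothesis, H0: p <= 0.80, is tested once, at the end, on all 29 patients. Stage I is a futility look only: with 7 or fewer of 9 successes the trial stops, with 8 or 9 it continues, and no claim of inferiority or superiority to p0 is made at stage I. With 26 or fewer of 29 successes H0 is not rejected, which by itself is not evidence of inferiority to 0.80 or 0.95. With 27 or more of 29, H0: p <= 0.80 is rejected; this does not show that the true rate is at least 0.95.

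Delete the clause that equates passing both limits with a true rate of at least p1. Report the observed rate with its interval beside either outcome.

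The cost is a few sentences. Recruitment and stopping counts are unchanged, and so are the error rates. The only loss is that each outcome carries a weaker label, which is the one the design supports.

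### The two-stage rule tests only whether freedom from steroid-resistant rejection exceeds 80%; the text wrongly reads passing as a true rate of at least 95% and boundary results as support for inferiority

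*Protocol article*

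**What the plan says.** The Protocol article, Sample size calculation, defines success as freedom from steroid-resistant rejection (SRR). The uninteresting and target success rates "have been fixed at 0.8 and 0.95 respectively". Stage I has 9 patients and stage II has 20, with boundaries r0 = 7 and r0 + r1 = 26. The section then gives the rule four meanings:

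- Stage I tests superiority to p0.
- "In stage II the rate will be compared to the actual target rate" p1.
- The boundary counts are introduced as "The maximum success rates that corroborate inferiority of the regimen to the fixed rates" p0 and p1.
- If more than 7 patients in stage I and 26 in stage II "do not experience a steroid resistant rejection the true response is at least the target level" p1.

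The Figure 2 caption describes the same design differently. It is "Derived from an optimal two-stage design for a phase II clinical trial", and r is the "maximum number of responders at which" H0 is not rejected.

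**The concern.** In an optimal two-stage design there is one hypothesis test, of H0: p ≤ p0. The target p1 enters only as the rate at which power is calculated. The text turns p1 into something the trial tests and proves, and turns non-rejection into a finding of inferiority. The figure caption does neither, so the two places disagree on what r means.

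This is the decision rule for the primary endpoint, and the article makes a phase III trial depend on the result. Read literally, 27 successes in 29 would license the statement that SRR is 5% or less, far below the 12.61% quoted for CNI-based regimens. The data would support only a rate below about 20%.

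**Working it through.** **Inputs.** From Sample size calculation and the Figure 2 caption: p0 = 0.80, p1 = 0.95, alpha = 0.05, beta = 0.2, n = 9 + 20 = 29, boundaries 7 and 26. The CNI reference is 12.61% SRR, so 100 − 12.61 = 87.39% success.

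**1. Reproduce the design.** The rule passes with at least 8 of 9 in stage I and at least 27 of 29 overall:

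P(pass | p) = P(X1 = 8)·P(X2 ≥ 19) + P(X1 = 9)·P(X2 ≥ 18), with X1 ~ Bin(9, p) and X2 ~ Bin(20, p).

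- p = 0.80: 0.3020 × 0.0692 + 0.1342 × 0.2061 = 0.0486.
- p = 0.95: 0.2985 × 0.7358 + 0.6302 × 0.9245 = 0.8024.

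These match the stated alpha and a power of 1 − 0.2. An exhaustive search for the smallest expected sample size at p0, with alpha ≤ 0.05 and power ≥ 0.80, returns the same design. The numbers are therefore correct, and they belong to a test of p ≤ 0.80.

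**2. Does passing show p ≥ 0.95?**

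- The lowest passing result is 27/29 = 93.1%, itself below 95%. Its two-stage one-sided 95% lower limit solves P(pass | p) = 0.05, giving p = 0.801.
- For 29/29 the limit solves p^29 = 0.05, so p = 0.05^(1/29) = 0.902. No possible result puts the lower limit at 0.95.
- The same formula gives these pass probabilities at true rates below the target:

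| True success rate | P(pass) |
|---|---|
| 85% | 15.8% |
| 87.39% (CNI reference) | 25.9% |
| 90% | 41.4% |
| just below 95% (0.9499) | 80.2% |

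Used as a test of p ≥ 0.95, the rule would have an error rate of about 80%.

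**3. Do boundary results corroborate inferiority?** Exact (Clopper-Pearson) 95% intervals, without adjustment for the two stages:

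| Result | Rate | 95% CI |
|---|---|---|
| 7/9 | 77.8% | 40.0% to 97.2% |
| 26/29 | 89.7% | 72.6% to 97.8% |

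Both intervals contain 0.80 and 0.95. The second estimate lies above p0 and above the CNI reference.

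**4. Does entering stage II show superiority to p0?** At p = 0.80, P(X1 ≥ 8) = 0.3020 + 0.1342 = 0.436. Stage I is passed 43.6% of the time when the regimen is exactly at p0, so it is a futility look.

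**5. A regimen equal to the CNI reference.** At p = 0.8739, P(stop at stage I) = P(X1 ≤ 7) = 0.317 and P(fail overall) = 1 − 0.2586 = 0.741, leaving 0.741 − 0.317 = about 0.425 failing at stage II.

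**6. The count for stage II.** Stage II enrols 20 patients, so 26 successes within it cannot occur. The notation r0 + r1 = 26 shows that a total out of 29 is meant.

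**The case against.** The strongest reply is that nothing operational is wrong. The sample sizes, boundaries, continue-or-stop action, alpha and power are all correct, the caption defines r properly, and the cumulative meaning of 26 can be recovered from the notation. The article also calls the study a pilot whose result must be confirmed in a randomised trial. All of that stands, and it limits the repair to wording. It does not make the conclusion about p1 valid.

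The other objections limit how far the point reaches:

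- **Inferiority to CNI.** A reader might infer from the 74.1% failure rate that a regimen equal to CNI would usually be declared inferior to CNI. The text does not say that: it speaks of inferiority to p0 and p1. For a true rate of 87.39%, inferior to p0 would be false (31.7%, stage I stops), but inferior to p1 would be true although not demonstrated (about 42.5%, stage II failures).
- **Failing results as evidence.** A reader might also infer that a failing result can never indicate inferiority. That is too absolute: 4/9 has an exact 95% upper limit of 78.8%, below p0, and 24/29 has 94.2%, below p1. Results at the stated boundaries are the ones that show nothing of the kind.
- **The other planned analysis.** The Statistical analysis plan section provides a non-inferiority test against the CNI reference with a margin of −0.1 (87.39 − 10 = 77.39%) and Agresti-Coull intervals. At 27/29 that 95% interval runs from about 77.0% to 99.2% and would be seen beside any claim. It is therefore not certain that a pass would be reported as proof of 95%. But that section does not correct the sentence, and it leaves open how two analyses of one endpoint fit together.

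**Conclusion.** The point holds as a wrong statement of what the primary decision rule shows. Crossing the boundary supports a success rate above 80% (SRR below 20%) at one-sided alpha 0.0486. It does not show 95% or more, and no outcome in 29 patients could. Not crossing means H0: p ≤ 0.80 was not rejected; at 7/9 or 26/29 this does not corroborate inferiority to either fixed rate. Entering stage II does not show superiority to p0. The 74.1% at the CNI reference is a failure rate and not a rate of false claims of inferiority to CNI.

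These figures assume independent patients with a common success probability, all 29 evaluable, and the boundaries applied as printed. The design itself is not in error.

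**What to change.** Bring Sample size calculation into line with the Figure 2 caption:

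- Describe stage I as a futility look with the existing boundary.
- State that H0: p ≤ 0.80 is rejected if more than 26 of all 29 patients, counted over both stages, are free of SRR.
- State that rejection supports only p > 0.80 (SRR below 20%) and not p ≥ 0.95.
- State that not crossing the boundary means H0 was not rejected and does not by itself show inferiority. Report the observed rate with its interval.
- Delete the sentences that conclude a rate of at least p1 and that treat the boundary counts as support for inferiority.
- State how this rule relates to the non-inferiority test against the CNI reference in the Statistical analysis plan section.

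The cost is wording only. No patient numbers, data or cut-offs change; the claim attached to a positive result becomes less favourable.
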